### Statistical analysis

Quantitative variables will be presented with mean and standard deviation, and qualitative variables will be shown in frequencies and percentages.

The Kolmogorov-Smirnov test will be used to compare the goodness of fit to a normal distribution of data from quantitative variables. For the contrast of bivariate hypotheses, the Student *t*-test will be performed for two means, while for qualitative variables, the Chi-Square and Fisher’s exact test will be used, when necessary. Likewise, for the analysis of three or more means, the ANOVA of repeated means will be used. On the other hand, the correlation between quantitative variables will be verified through the Pearson’s coefficient r. When the normality or homoscedasticity criteria are not met, non-parametric versions of the above tests will be performed.

Logistic regressions will be carried out to determine which variables can determine the improvement of the nutritional pattern and physical health through the FFQ (47), as well as blood and stool analytical values. Similarly, this analysis will be established concerning the psychopathological status through the PSP (46) and PANSS (45) scales, both of which have a discrete quantitative and nominal result values, according to established cut-off points and clinical interpretation. Raw and adjusted odds ratios will be calculated. Log-likelihood, the goodness of fit statistic, Cox and Snell R2, Nagelkerke R2, and Hosmer-Lemeshow tests should be used to assess the overall model fit. The exponentiation will be used to calculate the beta coefficients.

These multivariate tests will allow us to identify and adjust for the possible confounding effect of the independent variables on the outcome variables.

For all statistical analyses, an alpha error probability of less than 5% (*p* < 0.05) will be accepted, and the confidence interval will be calculated at 95%. The software SPSS (version 25.0) and EPIDAT (version 4.2) shall be used for the statistical analysis.

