### Selection of participants

For the assessment of the method’s effectiveness, a sample size of 22 individuals has been estimated (11 for the IG and 11 for the CG, with a power of 80% and a confidence of 95%, expecting a risk/prevalence difference of 63% post-intervention (48). The final size of 50 individuals has been established (25 for the IG and 25 for the GC) to minimize the effect of possible losses and the low study completion rates, especially in participants with significant negative symptoms. Participants who express a clear wish to participate voluntarily in the study will be assigned, through randomization in balanced blocks, to the IG or CG (Figure 1). Randomization will be conducted according to the results found in stool culture analysis (balancing the prevalence of dysbiosis in both groups). Concerning the established inclusion/exclusion criteria, these will be:

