#### Inclusion criteria

-Patients diagnosed on the spectrum of schizophrenia (without distinction by type), according to criteria DSM-5 and/or ICD-11.-Age between 18 and 65 years.-Absence of gastrointestinal comorbidity that contraindicates the use of prebiotics and/or probiotics (intolerance, explosive diarrhea, acute abdominal pain, etc.).-To show clinical stability for 6 months before the start of the study (absence of psychiatric hospitalization, maintenance of the level of functionality, and lack of social and occupational absenteeism).-To manifest agreement to participate in the study and to sign of informed consent (Supplementary Appendices I–III).

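### The logistic models of improvement leave the outcome's own baseline value out of the adjustment set, so covariates linked to a worse baseline can pass as determinants of improvement

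*Protocol article*

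**What the plan says.** All references are to the protocol article.

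- **Outcome.** Statistical analysis: "Logistic regressions will be carried out to determine which variables can determine the improvement of the nutritional pattern and physical health through the FFQ". The sentence goes on to blood and stool values. The next one extends the analysis to PSP and PANSS, "both of which have a discrete quantitative and nominal result values, according to established cut-off points and clinical interpretation". A logistic model needs a yes/no outcome.
- **Adjustment set.** The same section says the multivariate models adjust for confounding by the independent variables. The Independent variables section lists these as sociodemographic, therapeutic and clinical items. A cardio-metabolic diagnosis is among them; the baseline value of the outcome is not.
- **Who enters.** Inclusion criteria and Exclusion criteria require no abnormal FFQ, blood, anthropometric, stool, PANSS or PSP value. One criterion asks for stability: "To show clinical stability for 6 months before the start of the study (absence of psychiatric hospitalization, maintenance of the level of functionality".
- **Stool items.** Stool variables records the dysbiosis organisms as present or absent. Selection of participants balances the prevalence of dysbiosis between arms, which presupposes that some participants have it and some do not.
- **Baseline data.** Study design and Work plan (Block 1) collect PANSS, PSP, blood, FFQ and stool results at baseline.

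**The concern.** A participant who carries no dysbiosis organism at baseline cannot improve on that item. The same is true of anyone already on the good side of a cut-off, wherever improvement means crossing it. In a model fitted to all participants, these people are coded as not improved, together with participants who had an abnormality and did not respond.

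The models are meant to find which variables determine improvement. If the outcome mixes room to improve with response, a covariate that merely marks a bad baseline acquires an odds ratio above 1. A reader would take it as a predictor of who benefits from the diet. The baseline value is the variable that separates the two, and it is absent from the stated adjustment set.

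**Working it through.** The plan gives no figure on this point to reproduce. It states no baseline prevalence, no response rate and no correlation between covariates and baseline. All inputs below are assumptions, chosen to show direction and range.

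**1. Binary covariate, exact arithmetic.** Let a and b be the shares abnormal at baseline among participants with and without a cardio-metabolic diagnosis. Let r be the response rate among those able to improve, equal in both groups, so the true odds ratio is 1.0. If those unable to improve count as not improved, the observed rates are p = a × r and q = b × r, and OR = [p/(1−p)] / [q/(1−q)]. With r = 40%:

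| Abnormal at baseline, with v without | p | q | OR |
|---|---|---|---|
| 70% v 40% | 0.28 | 0.16 | (0.28/0.72)/(0.16/0.84) = 2.0 |
| 80% v 30% | 0.32 | 0.12 | (0.32/0.68)/(0.12/0.88) = 3.5 |

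A more extreme split of 90% v 20% gives (0.36/0.64)/(0.08/0.92) = 6.5.

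**2. How often this would be declared significant.** Fisher's exact test was enumerated for 50 participants, of whom 15 to 25 have the diagnosis. The false signal reaches p < 0.05 in about 10–15% of trials for OR 2.0 and 28–35% for OR 3.5 (57–65% for OR 6.5).

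**3. Continuous covariate, simulation.** Assumptions: 400,000 subjects; cut-off at the baseline median; baseline-to-end correlation 0.5 or 0.7; treatment effect 0.8 SD; a covariate correlated 0.5 with baseline and with no other link to the outcome. Odds ratios are per SD of the covariate, so they are not on the scale of step 1.

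| Model | Correlation 0.5 | Correlation 0.7 |
|---|---|---|
| Improvement (crossing), no baseline | 1.61 | 1.46 |
| Improvement, baseline value added | 1.00 | 0.99 |
| Restricted to those outside cut-off, no baseline | 0.82 | 0.74 |
| Restricted, baseline value added | 1.00 | 0.99 |
| Month-6 status, no baseline | 0.65 | 0.54 |
| Month-6 status, baseline status added | 0.83 | 0.75 |
| Month-6 status, baseline value added | 1.00 | 1.00 |

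Omitting baseline produces a false determinant in every version; only the direction changes. Restriction alone reverses the bias, because severity still varies among those outside the cut-off. A two-category baseline term removes part of the bias, and the measured value removes all of it.

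**The case against.** **Improvement is not defined as crossing a cut-off.** This is correct. Cut-offs are mentioned only for PSP and PANSS. FFQ results and the Lactobacillus and Bifidobacterium counts are continuous, so a change-based definition would leave improvement open to everyone, and the definition may sit in a fuller document. It is therefore too strong to say that the improvement outcomes in general cannot be reached. The presence/absence stool items remain a case that needs no assumed cut-off. The adjustment set is stated, not left open, and it omits baseline. Under a change definition, room for change would still depend on the baseline value.

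**The false signal may be small.** This also stands. The odds ratios rest on assumed splits, and at OR 2.0 few trials of 50 would show it as significant. A reader might infer that most determinants found will be baseline markers, but the documents do not allow that to be quantified.

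**The stability criterion proves little.** Maintained functioning is not a PANSS or PSP score within a cut-off, and it says nothing about diet or lipids. The point rests on the absence of any criterion requiring an abnormal value.

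**A tempting extension to the sample size fails.** A reader might infer that the planned difference shrinks, that at least 63% of participants must be abnormal at baseline, or that the stated power is lost. Selection of participants says only "expecting a risk/prevalence difference of 63% post-intervention". It names no endpoint or source population and does not link the figure to the logistic outcomes. A mixed source population would already contain any dilution. The 63% minimum is also false, because participants normal at baseline can worsen. With 50% abnormal at baseline, controls could end at 0.5 × 0.95 + 0.5 × 0.50 = 72.5% against 5% under intervention, a difference of 67.5 points. The planned 25 per arm would also absorb moderate dilution if few are lost.

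**Conclusion.** The concern holds as a fault in the stated adjustment set. The models of improvement adjust for listed covariates that do not include the outcome's baseline value, in a population where no abnormal value is needed for entry. Correlates of a worse baseline can therefore appear as determinants without affecting response.

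The mechanism is certain for presence/absence stool items. For other outcomes it follows if improvement means crossing a cut-off, which the text does not fix. The size is unknown: illustrative odds ratios run from about 1.5 (per SD, simulated) to 3.5 (binary covariate, 80% v 30% abnormal), where the true value is 1.0. No conclusion follows about the planned difference, the sample size or the power.

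**What to change.** In Statistical analysis:

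1. Include the baseline value of the outcome in every logistic model, alongside the listed independent variables. Use the measured value where there is one, and baseline status for presence/absence items.
2. Compare the arms in all participants on month-6 status (or value) adjusted for baseline status (or value), not on unadjusted improvement. For presence/absence items, month-6 status should also be the outcome in the determinant models. If baseline status is added to an improvement model there, one category has no events and its coefficient cannot be estimated.
3. Optionally add a supplementary improvement model restricted to participants outside the cut-off at baseline, again with the baseline value included where one is measured.

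The cost is analysis wording and one further term per model. The baseline data are already collected, and no visit or participant is added. The restricted model has fewer events and wider intervals, which is why it should be supplementary.

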#### Clinical variables

Type of psychotic disorder (nominal), duration of illness (continuous), age of first hospitalization (continuous), number of previous hospitalizations (discrete), number of previous relapses (discrete), number of previous suicidal behaviors (discrete), number of subsequent hospitalizations (discrete), number of subsequent relapses (discrete), number of subsequent suicidal behaviors (discrete), number of subsequent unscheduled consultations (discrete), substance abuse (nominal), type of substance (nominal), associated cardio-metabolic diagnosis (nominal).

Anthropometric measurements will be collected following the recommendations of the Manual of Standardized Anthropometry (49). Weight, height, and BMI shall be measured with an SECA^®^ 703s stadiometer and scale, with an accuracy of 0.1 kg and 0.1 cm, respectively. The abdominal perimeter shall be determined at the midpoint between the last rib and the iliac crest at the end of a normal expiration. The WelchAllyn^®^ ProBP 2,400 digital sphingomanometer shall be used for the study of blood pressure and heart rate.

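### Four event counts arising after study entry are listed among the variables the logistic models will adjust for as confounders, and the 23-variable adjustment list has no cap for 50 participants

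*Protocol article*

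**What the plan says.** The article sets out its independent variables under three subheadings: sociodemographic, therapeutic and clinical. The clinical list contains "number of subsequent hospitalizations (discrete), number of subsequent relapses (discrete), number of subsequent suicidal behaviors (discrete), number of subsequent unscheduled consultations (discrete"). The first three of these have counterparts in the same list that count previous events.

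The Statistical analysis section starts with between-group tests: t-test, chi-square or Fisher's exact test, repeated-measures ANOVA, and non-parametric versions. It then plans logistic regressions for improvement in diet and physical health (FFQ, blood and stool results) and in psychopathology (PANSS, PSP). "Raw and adjusted odds ratios will be calculated", and the purpose of the multivariable step is given as: "These multivariate tests will allow us to identify and adjust for the possible confounding effect of the independent variables on the outcome variables".

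That sentence uses the same term as the list's heading. It makes no exception for the later events and gives no limit on the number of covariates. Under Selection of participants: "The final size of 50 individuals has been established (25 for the IG and 25 for the GC").

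**The concern.** A confounder of the arm comparison has to precede assignment. Later relapses, admissions, suicidal behaviour and unscheduled visits come afterwards. On the protocol's own reasoning they could respond to the intervention: the Background links inflammatory changes to psychotic relapse, and the Discussion hopes to show a therapeutic effect on psychopathology. Holding such events fixed removes whatever benefit runs through them. If an unmeasured factor such as illness severity drives both the event and the outcome, it also makes the arms non-comparable within levels of the event. The adjusted odds ratios would then not describe the effect of being assigned to the intervention, although readers would take them that way.

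The length of the list is a second, conditional problem. Fifty participants cannot support a logistic model containing most of it.

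**Working it through.** **The plan's own figure.** The stated requirement is 22 participants (11 per arm) at 80% power and 95% confidence, "expecting a risk/prevalence difference of 63% post-intervention". The arm rates are not given. The two-sided pooled two-proportion formula with continuity correction gives 11 to 12 per arm for every control rate from 0 to 0.37. The stated number is therefore reproduced and is not in dispute. The sample that matters below is the planned 50.

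**Step 1: timing of the four counts.** The article does not define *subsequent*. It is set against *previous* for three of the four, and entry requires six months of stability without psychiatric admission. After study entry is the natural reading.

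**Step 2: can adjustment mislead?** This is an illustration with assumed inputs, none from the documents. Let u be an unmeasured severity factor, standard normal. Relapses are Poisson with mean 0.5·exp(0.5u) in controls and half that in the intervention arm. The log-odds of improvement are −0.2 − 0.8·(relapses) − 0.8u. All benefit runs through relapse and the direct effect is zero. With 1,000,000 records:

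- odds ratio for arm, unadjusted: 1.16
- adjusted for relapses: 0.92
- adjusted for relapses and u: 1.00, as constructed

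The true benefit disappears, and the value below 1 is collider bias. In milder settings, where some benefit bypasses relapse and there is no unmeasured factor, the odds ratio moves from 1.74 to 1.48 (relapses halved) or from 1.62 to 1.49 (relapses cut by 30%). These results show direction only.

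**Step 3: size of the list.** 7 sociodemographic + 3 therapeutic + 13 clinical = 23. With arm this is 24 parameters if each variable takes one degree of freedom, and more once nominal variables are coded. Events per parameter = size of the smaller outcome class ÷ parameters:

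- 50% outcome rate: 25/24 = 1.04
- 30% outcome rate: 15/24 = 0.62
- without the four later counts, 50% rate: 25/20 = 1.25

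**Step 4: separation, meaning no finite maximum-likelihood estimate.** There were 300 simulated data sets per cell, N = 50, half binary and half continuous independent covariates, each checked by linear programming:

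| Covariates besides arm | 50% rate | 30% rate | 20% rate |
|---|---|---|---|
| 23 | 49% | 80% | 93% |
| 19 | 13% | 38% | 74% |
| 10 | 0% | 3% | 18% |
| 5 | 0% | 2% | 8% |
| 2 | 0% | 1% | 6% |

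At N = 44 (an assumed 12% loss) the first row becomes 84%, 92% and 99%.

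A hand check is available for the 50% column. For n points in general position, k coefficients including the intercept, and an outcome that is a fair coin, Cover's counting formula gives P(separation) = P(Binomial(n − 1, ½) ≤ k − 1). With 23 covariates, k = 25 and P(Binomial(49, ½) ≤ 24) = 0.50 exactly, by symmetry. With 19, k = 21 and P(Binomial(49, ½) ≤ 20) = 0.13. With 5, k = 7 and the probability is below 0.0001. The simulation agrees.

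**The case against.** The strongest reply is that these models may not be the test of the intervention. The between-arm tests come first, and neither they nor the raw odds ratios condition on later events. The logistic models are introduced to find which variables go with improvement, and arm is never named as a term in them. This stands, and it limits the damage. It does not remove it, because the same section goes on to claim adjustment for confounding and to promise adjusted odds ratios.

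A reader might also infer that the plan fits a 23-covariate model that often cannot be estimated. The text does not say so. Its wording suggests that confounders are identified first and then adjusted for, and a selection rule is something an article may leave to a fuller document. The separation figures therefore apply only to full or near-full entry.

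A reader might further infer that a stated share of the effect would be lost. No relapse rate, and no effect of relapse on any outcome, appears in the documents. The main objective is nutritional and cardio-metabolic, where the influence of relapse is unknown.

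Finally, it would go too far to say that randomisation leaves adjustment without purpose. With 25 per arm, chance imbalance is plausible and baseline adjustment can add precision. If the models are predictor models, randomisation does not remove confounding among the predictors.

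None of these replies justifies treating the four later counts as confounders. A later analysis plan would have to reverse that classification, not merely add detail to it.

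**Conclusion.** The point holds in a limited form and should be fixed. By the article's own labels, four post-entry event counts fall within the set to be adjusted for as confounders. Following that rule can bias the adjusted odds ratios, by an amount the documents do not allow one to quantify. This rests on reading *subsequent* as after study entry, and on the events being affected by the intervention or sharing unmeasured causes with the outcome.

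The list of 23 is too long for 50 participants if all or most of it is used: about one event per parameter at best, and separation in about half of data sets at a 50% outcome rate, more at lower rates. The simulation assumes independent covariates with one degree of freedom each. With five or fewer covariates the problem largely goes away.

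The documents do not support the conclusion that the trial's treatment comparison as a whole is invalid, because the unadjusted analyses are untouched.

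**What to change.** - Remove the four *subsequent* counts from the independent variables and report them as outcomes by arm.
- For treatment comparisons, fix the model as arm, the baseline value of the outcome, and the dysbiosis factor that randomisation balances. Neither of the last two appears in the present list. This is three parameters, so 25/3 = 8.3 events per parameter at a 50% outcome rate and 15/3 = 5 at 30%.
- Use the other baseline variables to describe the sample, or in small models labelled exploratory. Removing the four counts alone is not enough, since 19 covariates still give separation in 13% to 74% of runs.
- State when the reason for a change of antipsychotic is recorded. If it can arise after randomisation, keep it out of the adjustment set too.

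The cost is rewording the analysis section and moving four variables, with no extra participants, visits or data. The downside is that no large multivariable predictor model would be fitted. At 10 events per parameter, a rough guide, the full set would need 24 × 10 ÷ 0.5 = 480 participants at a 50% outcome rate.

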## Methods/design

### Study aims

#### Main objective

Determination of the nutritional and cardio-metabolic efficacy of a prebiotic and probiotic dietary intervention in patients with schizophrenia spectrum disorders.

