### Study variables

#### Result variables

##### Clinical efficacy of prebiotic/probiotic dietary modulation

-Scale for Positive and Negative Schizophrenia Syndrome (45) (categorized PANSS): discrete.-Personal and Social Functioning Scale (46) (categorized PSP) outcome: discrete.

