##### Blood test variables

-*Hematological profile*: Red blood cells (x10e^6^/mm^3^, continuous), hemoglobin (g/dL, continuous), hematocrit (%, continuous), M.C.V. (fL, discrete), H.C.M. (pg, discrete), C.H.C.M. (g/dL, discrete), R.D.W (%, continuous), leukocytes (×10e^3^/mm^3^, discrete), neutrophils (×10e^3^/m, continuous), lymphocytes (×10e^3^/m, continuous), monocytes (×10e^3^/m, continuous), eosinophils (×10e^3^/m, continuous), basophils (×10e^3^/m, continuous), platelets (×0e^3^/mm^3^, discrete), M.P.V. (fL, discrete). See Table 1 for abbreviations corresponding to the blood test variables.

**TABLE 1 T1:** Blood test variables: Abbreviations.

	Abbreviation	Meaning
Hematological profile	M.C.V	Mean corpuscular volume
	H.C.M	Mean corpuscular hemoglobin
	M.C.H.C	Mean corpuscular hemoglobin concentration
	R.D.W	Red cell distribution width
	M.P.V	Mean platelet volume
Biochemical profile	ALT	Alanine transaminase
	GPT	Glutamic pyruvic transaminase enzyme
	G-GT	Gamma-glutamyl transferase
	ALP	Alkaline phosphatase
	Na^+^	Sodium
	K^+^	Potassium
	Cl^–^	Chlorine
	Ca^2+^	Calcium
	HbA1c	Glycosylated hemoglobin
	IFCC	International federation of clinical chemistry and laboratory medicine
	Fe^2+^	Iron
	FRT	Ferritin
	LDH	Lactate dehydrogenase
	C-HDL	High-density lipoprotein
	C-LDL	Low-density lipoprotein
	TSH	Thyroid stimulating hormone
	PRL	Prolactin
	LUES	Syphilis
	HCV	Hepatitis C virus
	HAV	Hepatitis A virus
	HIV	Human immunodeficiency virus

-*Biochemical profile.* ALT/GPT (IU/L, discrete), G-GT (IU/L, discrete), FAL (IU/L, discrete), Na^+^/K^+^ (mEq/L, discrete/continuous, respectively), Cl^–^ (mEq/L, continuous), Ca^2+^ (mEq/L, continuous), urate (mg/dL, continuous), glucose (mg/dL, discrete), HbA1c (%, continuous), HbA1c IFCC (mmol/mol, continuous), fructosamine (mcmol/L, discrete), creatinine (mg/dL, continuous), Fe^2+^ (mcg/dL, discrete), FRT (mcg/dL, discrete), folate (mcg/dL, continuous), vit.B12 (ng/mL, discrete), vit.D total (D2 + D3) 25-OH (ng/mL, discrete) cholesterol (mg/dL, discrete), triglycerides (mg/dL, discrete), LDH (IU/L, discrete), C-HDL (mg/dL, discrete), C-LDL (mg/dL, discrete), total cholesterol/C-HDL (mg/dL, discrete), glomerular filtrate estimation (mL/m/173, discrete), TSH (mU/L, continuous), PRL (ng/dL, continuous), LUES (IU/L, nominal/discrete), a-HAV-M (IU/L, nominal/discrete), a-HCV (IU/L, nominal/discrete), HBsAg (UI/L, nominal/discrete), a-HBC-IgG (UI/L, nominal/discrete), a-HBs (UI/L, continuous), a-HIV (mcL, nominal/discrete).

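### No primary outcome is named and p<0.05 is accepted for every analysis over about 68 listed variables, so an efficacy conclusion would have no controlled false-positive rate

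*Protocol article*

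**What the plan says.** - **Significance rule** (Statistical analysis): "For all statistical analyses, an alpha error probability of less than 5" per cent is accepted. No ranking of outcomes accompanies it.
- **Main objective:** "Determination of the nutritional and cardio-metabolic efficacy of a prebiotic and probiotic dietary intervention in patients with schizophrenia spectrum disorders". This covers two domains and names no variable.
- **Outcomes:** the first list, headed clinical efficacy, opens with "Scale for Positive and Negative Schizophrenia Syndrome" and also holds the PSP. Sibling lists follow for diet, anthropometry, haematology and biochemistry, with stool culture under a heading of its own. Height and seven infection serologies are included, and HbA1c appears in two units: "HbA1c (%, continuous), HbA1c IFCC (mmol/mol, continuous".
- **Sample size** (Selection of participants): a calculated total of 22, split equally between the arms, is justified by the words "with a power of 80% and a confidence of 95%, expecting a risk/prevalence difference of 63% post-intervention". The total is then raised to 50, or 25 per arm, to allow for losses. The outcome to which the 63% refers is not stated.
- **Judging effectiveness:** Block 3 of the Work plan looks at nutritional, cardio-metabolic and psychopathological change together. The Discussion expects to show a significant improvement, and evidence strong enough to establish nutritional management as an effective treatment.

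**The concern.** A sample size and a significance level acquire meaning through the outcome they serve. Here the sample size points to an unidentified binary outcome, the main objective to two domains, and Block 3 to three. The 5% level applies to everything. A chance result in any one measure would meet the stated rule and could carry the conclusion that the Discussion anticipates. With 50 participants and no ranking of outcomes, nothing in the article prevents that.

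**Working it through.** **1. The plan's own figure.** The inputs are a difference d = 0.63, 80% power and 95% confidence. The arm rates are not given, so the control rate p2 was varied from 0.01 to 0.36 (assumption), with p1 = p2 + 0.63.

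n per arm = [1.96·√(2·p̄·(1−p̄)) + 0.8416·√(p1(1−p1) + p2(1−p2))]² / d²

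- Two-sided without continuity correction: 8–9 per arm.
- With correction, n′ = (n/4)·[1 + √(1 + 4/(n·d))]²: 11–12 per arm, or 22–24 in total.

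The stated 11 per arm is therefore reproducible as a comparison of two proportions, if a correction was used. An intended binary outcome presumably exists; the article does not say which.

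**2. Count of listed variables.** 2 scales + 2 diet (FFQ counted once) + 7 anthropometric + 15 haematological + 34 biochemical and serological (Na and K counted separately) + 8 stool = 68. Without the stool block it is 60.

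**3. Upper bound.** Take one test per variable, independent, each at exactly 5%, with no true effect.

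- Expected false positives: 68 × 0.05 = 3.4.
- At least one, either direction: 1 − 0.95^68 = 96.9%.
- At least one, favourable direction: 1 − 0.975^68 = 82.1%.

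**4. Allowing for correlation.** In 40,000 simulated sets of normal test statistics, a common correlation was assumed within each of the six groups in step 2 and none between groups. The 53-variable set drops height, the seven serologies, the six pathogens and the duplicate HbA1c: 68 − 1 − 7 − 6 − 1 = 53.

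| Assumed correlation | 68 variables: either / favourable | 53 variables: either / favourable |
|---|---|---|
| 0.3 | 93% / 68% | 88% / 61% |
| 0.5 | 86% / 58% | 80% / 51% |
| 0.7 | 74% / 46% | 68% / 41% |

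As a stress case, one correlation of 0.7 across all 68 variables gives 44% / 22%.

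**5. Only variables plainly in the three domains.** PANSS and PSP (2), FFQ and culinary knowledge (2), anthropometry without height (6), glucose, HbA1c once and fructosamine (3), and lipids (5) make 18. Adding iron, ferritin, folate, B12 and vitamin D makes 23. If independent:

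- Either direction: 1 − 0.95^18 = 60%; 1 − 0.95^23 = 69%.
- Favourable direction: 1 − 0.975^18 = 37%; 1 − 0.975^23 = 44%.

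**6. Comparison.** One named primary outcome at two-sided 5% gives 5% in either direction and 2.5% in the favourable one.

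**The case against.** The strongest reply has four parts.

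- **Not every listed variable is said to be an efficacy test.** A reader might infer that all 68 are compared between arms and that a false claim of efficacy is nearly certain. The Statistical analysis section does not say so. It matches tests to variable types, then names FFQ, blood and stool values, PSP and PANSS as modelled outcomes. Height and infection serology may simply be collected data. This stands, and it makes 97% an upper bound only.
- **Independence at a full 5% is unrealistic.** Weight and BMI, haemoglobin and haematocrit, the cholesterol measures, and the two HbA1c units nearly duplicate each other. Rare binary items under Fisher's exact test reject well below 5%: with 25 per arm, 5 versus 0 gives p = 2·C(25,5)/C(50,5) = 0.0502. This also stands and lowers the figure. Other features raise it: the FFQ yields several nutrients and food groups, and both raw and adjusted odds ratios are planned. Repeated visits need not multiply the count, because repeated-measures ANOVA can pool them.
- **The clinical efficacy heading might be read as contradicting the main objective.** It is weak evidence of that. Psychopathological impact is a specific objective in its own right, and the heading is one of several at the same level.
- **Multiplicity rules often sit in a SAP, which is not shown.** A missing correction would not be a finding by itself. But the article does state a rule, 5% for all analyses, and it gives a sample size without saying for which outcome. Those are statements in this document, not details left for later.

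**Conclusion.** The point holds. The article names no primary outcome, leaves the outcome behind its 63% difference unidentified, and accepts p<0.05 throughout while intending to conclude efficacy. The false-positive chance cannot be given as one number, because it depends on which variables count as efficacy tests and how correlated they are. The upper bound is about 97%. Assumed within-domain correlations of 0.7 down to 0.3 give about 74–93% over all 68 variables. The 18–23 variables plainly in the named domains give about 60–69% if independent (37–44% favourable), and less with correlation. Each figure is many times the 5% (2.5% favourable) that one named primary outcome would give. Near-certainty of a false efficacy claim is not supported; an uncontrolled error rate is.

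**What to change.** - **Primary outcome:** name one nutritional or cardio-metabolic measure already collected, at 6 months, tested at two-sided 5%. Use either the outcome on which the sample size was calculated, stated explicitly, or another measure (HbA1c or abdominal circumference, for example) with the power statement restated for it at the planned 25 per arm. For a continuous primary with complete data, the normal approximation gives a detectable standardised difference at 80% power of (1.96 + 0.84)·√(2/25) = 0.79.
- **Secondary outcomes:** name a short list, such as FFQ fibre, PANSS total, PSP and LDL, and test it with Holm.
- **Everything else:** report with 95% confidence intervals as exploratory.
- **Tidy the list:** treat height and infection serology as baseline data, and count HbA1c once.

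No extra data, visits or participants are needed. The cost is that nominally significant results outside the short list can no longer be claimed as efficacy, and the power statement may have to be rewritten.
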